### Number of Participants

From previous studies that showed significant results in terms of efficacy it appears that the minimal number of patients in parallel design was 50 (2). This was the case for behavioral ABA approach [e.g., Ref. (6)] or for developmental ESDM approach [e.g., Ref. (3)]. The number of patients to enroll was based on the following theoretical statistics estimation: for a moderate effect size (α = 0.6), a power fixed at 80%, and a level of significance for a *p*-value fixed at <0.05, 80 patients randomized into two groups are required for a student *t*-test. Given our choice to use linear mixed models (see below) to take into account participant’s effect, we planned to recruit from 70 to 80 participants.

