### Statistical Analysis

Statistical analyses will be performed using R Software, Version 2.12.2. To assess whether improvement occurs in both primary and secondary variables, we will use linear mixed models with change in a given variable explained by group exposure (DS1-EI vs. TAU), time (baseline vs. 18 vs. 36 months) and their interaction (group exposure × time). We will also include a random effect and a site effect. This should account for individual heterogeneity, site heterogeneity, variable scores at inclusion, and change specific to DS1-EI within the same statistical regression. For missing data when available, we will use the last observation carried forward. In case of a non-Gaussian distribution, we will study the log transformation (or other transformation when appropriate) to achieve a normal distribution. Lost or drop-out patients will also be compared between groups using a separate non-parametric comparison.

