## Discussion

We hope that the current trial will help demonstrate the feasibility of adapting and task-shifting a group of interventions used primarily as early interventions for autism to a school-based context and for use with older individuals with autism and intellectual disabilities. The school-based intervention program [the developmental and sequenced one-to-one educational intervention (DS1-EI)] was adapted from several methods including TEACCH (4, 5), ESDM (3), and ABA (6, 37). The key principles of the method are the intensity, the regular assessments and updating of objectives, the encouragement of spontaneous communication, promotion of skills through play with peers, support of positive behaviors instead of tackling challenging behaviors, regular team supervision, capitalization on teachers’ unique skills, and developmental and sequenced learning (2). The use of sequenced learning (i.e., teacher and activity change every 10–15 min to keep the child’s attention in the context of an anticipated time agenda) is likely the most original proposal. We are aware that treating children with autism and ID is very challenging. The effect sizes are typically small. To balance this risk of failure, we chose to have a rather long study duration with two single-blind assessments at 18 and 36 months. Given the number of sites, which may have introduced bias, we are satisfied that we did not find differences between the groups at baseline.

We are aware that there are several limitations to this trial. First, given the severity of the patients’ conditions, the study duration and the nature of the intervention, only a single-blind for the primary variables was feasible. Second, the method used to randomize participants (to limit the bias of TAU) combined with the study duration and the supervision of local teams is likely to modify local staff practice and to lead to some DS1-EI principles being used in the TAU group as well. Third, because our public sponsors required us to balance hospital/academic/large city sites and non-hospital/remote rural area sites, we cannot assume that we will achieve a uniform level of adherence to the program from one site to another. Finally, given the study duration, we do not know whether we will retain a sufficient number of patients in the program to maintain the statistical power needed for per protocol analyses.

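### The 80% t-test power is stated with no allowance for loss over 36 months, and the 75 enrolled children do not deliver it

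*Protocol article*

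**What the plan says.** In the protocol article, Number of Participants, the calculation is "for a moderate effect size (α = 0.6"), with "a power fixed at 80"% and a significance level "fixed at <0.05". The result is that "80 patients randomized into two groups are required" for a t-test. The section then says, with the use of linear mixed models as its only reason, that "we planned to recruit from 70 to 80 participants". It mentions neither retention nor a loss rate.

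Other sections bear on follow-up:

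- Participants and Recruitment sets the trial duration at 36 months. It excludes families who plan a change of institution only where that change is near.
- Table 3 shows CARS and PEP-3 measured at inclusion, month 18 and month 36 only.
- Statistical Analysis plans a mixed model over those three times, with carry-forward of the last value for missing data. It adds that "Lost or drop-out patients will also be compared between groups".
- The Discussion says "we do not know whether we will retain a sufficient number of patients in the program to maintain the statistical power needed". That sentence goes on to name per protocol analyses as the ones affected.
- The Abstract reports 75 children enrolled, 38 in the DS1-EI group and 37 in the TAU group.

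**The concern.** A t-test sample size counts children who have an outcome. Here that count is also the most that the trial planned to recruit, so the calculation as written leaves no room for loss. Three years is a long follow-up, and the article foresees drop-outs.

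What is at stake is how the result is read. The Discussion says that effects in this field are usually small, so a null result is a real possibility. A reader who takes the printed 80% at face value would then overrate how strongly the trial speaks against an effect of 0.6.

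**Working it through.** **Inputs.** From Number of Participants: standardised effect d = 0.6 (printed with the symbol α, read here as a standardised mean difference), power 80%, significance 0.05, two-group t-test, stated total 80. From the Abstract: 38 and 37 randomised. Two assumptions are needed. The test is taken as two-sided, since the article does not say. Loss is taken as 0 to 30%, equal in both groups, since no rate is given.

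**Formula.** With n₁ and n₂ children analysed, the noncentrality is δ = d·√(n₁n₂/(n₁+n₂)) on n₁+n₂−2 degrees of freedom. Power is the probability that a noncentral t with that δ lies outside the two-sided 5% critical values.

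**The article's own figure.** The normal approximation gives 2(1.960 + 0.842)²/0.6² = 43.6, so 44 per group and 88 in total. The exact t calculation gives 45 per group, or 90. One-sided at 5%, the totals are 70 and 72. None of these is 80. With 40 per group, δ = 0.6·√20 = 2.68 and two-sided power is 75.5%. So 80 complete children reach 80% power only for an effect of about 0.63.

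**The enrolled sample.** With 38 and 37, n₁n₂/(n₁+n₂) = 1406/75 = 18.75, so δ = 0.6·√18.75 = 2.60 on 73 degrees of freedom, and power is 72.7%. If a fraction f is lost in each group, δ is multiplied by √(1−f):

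| Assumed loss | Children with outcome | δ | Power at d = 0.6 | Cost of loss alone | Effect detectable at 80% power |
|---|---|---|---|---|---|
| 0% | 75 | 2.60 | 72.7% | – | 0.66 |
| 10% | 67.5 | 2.46 | 68.0% | 4.7 points | 0.69 |
| 20% | 60 | 2.32 | 62.7% | 10.0 points | 0.74 |
| 30% | 52.5 | 2.17 | 56.8% | 15.9 points | 0.79 |

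**Separating the two causes.** The step from 80% to 72.7% involves no attrition. About 4.5 points (80% to 75.5%) come from 80 not matching the stated inputs, and 2.8 points (75.5% to 72.7%) from enrolling 75. Only the fifth column belongs to loss.

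The cost of loss does not depend on the formula problem. Suppose 80 complete children did give 80% power, which means an effect of about 0.63. Losing 10% or 20% of them would still leave 75.6% or 70.5%.

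**The case against.** Five points can be made on the other side.

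1. **An allowance may be built in.** A one-sided 5% t-test needs 72 children, and 72/0.9 is exactly 80. This fits, but the article states neither a one-sided test nor a loss rate. So one can say that no allowance is stated, not that none was made. Even on this reading, the 75 enrolled give 78.6% after 10% loss and 74.3% after 20%.

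2. **The doubt about retention is narrower than it looks.** It concerns staying in the program and per protocol analyses. It should not be read as an admission that the analysis of all randomised children lacks power. This stands. The planned comparison of drop-outs still shows that loss to the trial is foreseen.

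3. **The planned analysis is not a t-test.** A child lost after month 18 contributes real 18-month data, and baseline information can recover power. If the correlation between baseline and endpoint were 0.5 (assumed), a baseline-adjusted comparison of the 75 would have about 84% power, with 80% after 10% loss and 75% after 20%. At 0.3 the figures are about 77%, 72% and 67%; at 0.7, about 95%, 93% and 89%. This stands as a limit on the point: the article gives no correlation, so neither a shortfall nor a recovery is shown for the mixed model.

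4. **Carry-forward keeps every child in the analysis.** It keeps the count but not the information. A child lost before month 18 would carry the baseline CARS or PEP-3 forward as zero change, which tends to dilute a difference. The amount depends on when children leave and on the spread of change, neither of which the article gives, so no single figure is defensible.

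5. **Enrolment is complete and the article lists retention as a limitation.** Both are true, and they keep the point minor. The power statement is still printed without the qualification.

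**Conclusion.** The point holds for the t-test power statement. The number called required is also the recruitment ceiling, no loss allowance is stated, and the enrolled sample does not have the stated power. At d = 0.6, two-sided 0.05, the 75 children give about 73% with complete follow-up, 68% at 10% loss and 63% at 20%. The share due to attrition is about 5 and 10 points; the rest is the sample-size discrepancy and enrolment below 80. These figures rest on a two-sided test, equal loss in both groups and loss rates chosen for illustration.

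A reader might infer that the planned mixed-model analysis falls below 80% power. The article does not support that, because the answer turns on a within-child correlation that it does not give. The importance is low: the analysis and its validity are untouched, and what changes is how much weight a null result can bear.

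**What to change.** In Number of Participants, state that the calculated number means children with outcome data at 36 months. Replace the single 80% with the power and the detectable effect of the 75 enrolled over a stated, assumed retention range. For retention of 80 to 100%, the two-sided t-test figures are 63 to 73% power at d = 0.6, and a detectable effect of 0.74 down to 0.66. If the authors wish to claim more power for the mixed model, they should state the correlation they assume and give the power that follows from it.

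No further enrolment and no change to the analysis is needed. The only cost is a less favourable power statement.

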**Discussion and baseline description:**

We enrolled 75 participants: 38 were randomized to the DS1-EI and 37 to the TAU groups. At enrollment, we found no significant differences in participants’ characteristics between groups. As expected, exposure to school was the only significant difference [9.4 (±4.1) h/week in the DS1-EI group vs. 3.4 (±4.5) h/week in the TAU group, Student’s *t*-test, *t* = 5.83, *p* < 0.001].

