### Participants and Recruitment

All participants were recruited in outpatient French health care institutions that are specialized in treating children with autism and intellectual handicaps. At the request of the French national health regulatory authority [*Agence nationale de sécurité du médicament et des produits de santé* (ANSM)] and the main sponsor [*Caisse Nationale de Solidarité pour l’Autonomie* (CNSA)], we balanced day care hospitals and special education clinics to have a representative sample of French institutions. In each institution, we obtained a specific commitment to accept the implementation of a DS1-EI school-based program as described below and to recruit the same number of participants to be randomized into a DS1-EI exposed group (called the DS1-EI group) or a treatment as usual (TAU) group who would serve as controls. The commitment also entailed having the required resources from local school authorities to implement the DS1-EI and to have the leading teacher from the classroom be supervised. To avoid bias in the TAU group as a result of the diversity of institutions, we decided to randomize participants by site. Figure 1 summarizes the list of institutions involved in the protocol and the number of patients by site. In total, we enrolled 75 participants.

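### The stated requirement of 80 patients does not follow from its own inputs (a two-sided t-test needs 90), and 80% power for the planned 70–80 is not shown

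*Protocol article*

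**What the plan says.** The sample size rests on one short paragraph of the protocol article, Number of Participants. It sets its inputs as "for a moderate effect size (α = 0.6), a power fixed at 80" per cent, and a significance level with the p-"value fixed at <0.05". From these it concludes that "80 patients randomized into two groups are required for a student" *t*-test. It then refers to the choice of linear mixed models and says "we planned to recruit from 70 to 80 participants". It gives no sidedness, no within-child correlation and no power figure for the 70 to 80 range.

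On allocation, Participants and Recruitment says that each institution committed to "recruit the same number of participants to be randomized into a DS1-EI exposed group" or a treatment-as-usual group, so the ratio is 1:1. The Abstract reports the result of recruitment: "We enrolled 75 participants: 38 were randomized to the DS1-EI and 37 to the TAU groups".

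**The concern.** The paragraph names a test, an effect size, a power, a significance level and a resulting number, so it can be checked directly. A two-sided t-test at a standardised difference of 0.6 is well known to need somewhat more than 40 per arm, so a total of 80 looks low. The target is then allowed to fall to 70 with a reference to the mixed model but no figure for what that model gains.

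This paragraph is the only justification of trial size in the article. A reader who takes it at face value will believe that 80 patients give 80% power to detect 0.6 on a t-test, and that 70 to 80 do so under the mixed model. The first is wrong on the usual reading and the second is not demonstrated. Both bear on how a non-significant result would be read.

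**Working it through.** **Inputs**

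- Standardised difference *d* = 0.6, power 80%, significance level 0.05, two-sample Student t-test, stated total 80: Number of Participants.
- Equal allocation: Participants and Recruitment.
- Planned 70 to 80: Number of Participants. Enrolled 75 (38/37): Abstract.
- Sidedness: not stated. Two-sided is assumed. Table 4 supports this: for the CARS, *t* = 0.67 is reported with *p* = 0.504, and the two-sided p-value for 0.67 on 38 + 36 − 2 = 72 degrees of freedom is 0.505.

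**Step 1. Try to reproduce 80**

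Normal approximation, per arm: n = 2(z₁₋α/₂ + z₁₋β)² / d².

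- Two-sided: 2(1.960 + 0.8416)² / 0.36 = 43.6, so 44 per arm, 88 in total.
- One-sided: 2(1.645 + 0.8416)² / 0.36 = 34.4, so 35 per arm, 70 in total.

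Exact t-test (noncentral t):

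- Two-sided: 44.6 per arm, so 45 per arm, **90 in total** (power 80.4%).
- One-sided: 35.04 per arm, so 36 per arm, **72 in total**.

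Neither gives 80. The figure is reached only with an input that the paragraph does not state: two-sided with 75% power instead of 80%, or one-sided with 10% added for dropout (72 / 0.9 = 80).

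**Step 2. Power of the sizes named, two-sided t-test, d = 0.6**

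Noncentrality = d √(n₁n₂ / (n₁ + n₂)), with n₁ + n₂ − 2 degrees of freedom.

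| Total (arms) | Noncentrality | Power | d detectable with 80% power |
|---|---|---|---|
| 80 (40/40) | 0.6 × √20 = 2.683 | 75.5% | 0.63 |
| 75 (38/37) | 0.6 × √18.75 = 2.598 | 72.7% | 0.66 |
| 70 (35/35) | 0.6 × √17.5 = 2.510 | 69.7% | 0.68 |
| 90 (45/45) | 0.6 × √22.5 = 2.846 | 80.4% | 0.60 |

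On a one-sided 5% test, 38/37 would have 82% power.

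**Step 3. What the mixed model could add**

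The article gives no correlation, so every *r* below (baseline to follow-up) is an assumption. The effect of 0.6 is taken in units of the raw-score SD, and the effective difference is 0.6 divided by the square root of the variance factor.

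- Baseline as a level of time, group-by-time change contrast: variance factor 2(1 − r).
  - r = 0.5: factor 1.0, effective d = 0.6, power at 38/37 = 72.7% (no gain).
  - r = 0.6: factor 0.8, effective d = 0.671, power about 82%.
- Baseline as a covariate: variance factor 1 − r².
  - r = 0.3: factor 0.91, effective d = 0.629, power about 77%.
  - r = 0.5: factor 0.75, effective d = 0.693, power about 84%.

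The Statistical Analysis section lists time as baseline, 18 and 36 months with a group-by-time interaction, which points to the first form. It also says that the model accounts for scores at inclusion, so the specification is open to some reading. Whether 75 patients reach 80% depends on both choices.

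**The case against.** The strongest reply is that the t-test is not the planned analysis. The article gives no power for 70 to 80 and bases that range on a mixed model, which can be more efficient. This stands. A reader might infer from the t-test that the trial lacks 80% power, but Step 3 shows that the model could recover it, so the article supports only the weaker statement that 80% power is not shown.

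Sidedness is also unstated, and on a one-sided 5% test 75 patients would have 82%. This stands as a limit on the size of the shortfall. It does not rescue 80 as the required number, which would then be 72.

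It can also be said that an article leaves correlation and dropout assumptions to the full protocol. That is fair, and their absence is not itself the point. The point is that a stated figure does not follow from its stated inputs, and the range planned after it cannot be checked.

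Three further inferences are tempting and should not be drawn:

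- The Discussion says "The effect sizes are typically small", which may seem to contradict planning on 0.6. The authors go on to name the long study duration as their response to that risk. An optimistic planning value is a judgement, not a contradiction.
- One might cut the 75 by a loss rate and quote lower power. The article gives no such rate, and it plans last observation carried forward, so children lost after an assessment can remain in the analysis.
- The symbol α beside the effect size is a slip of notation; the words next to it make the meaning clear.

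**Conclusion.** The figure of 80 is wrong as written. With the stated inputs and a two-sided test, the requirement is 90, and 80 gives 75.5% power, a shortfall of 10 patients or 4.5 percentage points. The arithmetic is certain; the two-sided reading is an assumption, supported by the article's own tests. On the same t-test the enrolled 75 have 72.7% power and can detect 0.66 with 80% power.

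For the planned mixed model, 80% power is neither shown nor refuted. Under the assumed correlations in the working, 38/37 gives between about 73% and about 84%.

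This should be fixed. It affects how the trial's size is described and how a null result is read, not the conduct of the trial or the validity of its comparison.

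**What to change.** Revise the Number of Participants paragraph; no further enrolment is needed.

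1. Either correct 80 to 90, or state that 80 patients give about 75% power at d = 0.6 (80% at d = 0.63) and that the 75 enrolled give about 73% (80% at d = 0.66), on a two-sided 5% t-test.
2. State the sidedness. If the calculation was one-sided or included a dropout allowance, say so and give the figures.
3. If the mixed model is the reason for 70 to 80, give the power under the group-by-time model actually specified, with the assumed within-child correlation and a statement of whether baseline is a time level or a covariate.
4. Label the effect size *d*, and keep α for the significance level.

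The cost is one paragraph of wording and a slightly less favourable t-test power figure.

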### Statistical Analysis

Statistical analyses will be performed using R Software, Version 2.12.2. To assess whether improvement occurs in both primary and secondary variables, we will use linear mixed models with change in a given variable explained by group exposure (DS1-EI vs. TAU), time (baseline vs. 18 vs. 36 months) and their interaction (group exposure × time). We will also include a random effect and a site effect. This should account for individual heterogeneity, site heterogeneity, variable scores at inclusion, and change specific to DS1-EI within the same statistical regression. For missing data when available, we will use the last observation carried forward. In case of a non-Gaussian distribution, we will study the log transformation (or other transformation when appropriate) to achieve a normal distribution. Lost or drop-out patients will also be compared between groups using a separate non-parametric comparison.

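### The planned group-by-time contrast handles inclusion scores by subtraction, not by conditioning on them, and so gives up precision that baseline adjustment would recover at no cost

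*Protocol article*

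**What the plan says.** The Statistical Analysis section of the protocol article describes "linear mixed models with change in a given variable explained by group exposure (DS1-EI vs. TAU), time (baseline vs. 18 vs. 36 months") together with the interaction of group and time. It continues: "We will also include a random effect and a site effect". No covariate for the inclusion score appears among the terms, and nothing constrains the two arms to a common baseline mean.

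The section then states what the model is expected to do: "This should account for individual heterogeneity, site heterogeneity, variable scores at inclusion, and change specific to DS1-EI". For non-normal data it offers a fallback: "we will study the log transformation (or other transformation when appropriate) to achieve a normal distribution". Missing values are to be filled by last observation carried forward where one exists.

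**The concern.** Two features of the model sit awkwardly together. The response is called change, yet baseline is one of the three time levels, so the response is not clearly defined. The text also expects the model to take care of inclusion scores, but the listed terms do so only by differencing. A reader could take the plan to deliver a baseline-adjusted effect when it delivers a comparison of mean changes.

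Precision is what is at stake. The trial enrolled 75 children, the Discussion expects small effects, and the authors are unsure that they will keep enough participants for adequate power. Conditioning on a score that is already measured recovers precision without recruiting anyone. It also removes the part of the estimate that depends on which arm happened to start worse.

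**Working it through.** **Inputs.** From the abstract: 38 children in DS1-EI and 37 in TAU. From Table 4: CARS 41.3 (SD 7) vs 40.2 (SD 7.1), and PEP-3 imitation 23.1 (SD 7.8) vs 25.8 (SD 6.7). From Number of Participants: "for a moderate effect size (α = 0.6), a power fixed at 80"%, significance level 0.05, 80 patients, Student t-test. The 0.6 is read as a standardised difference. The correlation r is not in the documents and is varied from 0.3 to 0.9. Equal SDs at baseline and 36 months are assumed.

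**The plan's own figure.** A t-test at 0.6 with 80% power needs 90 patients in total two-sided (88 by the normal approximation) or 72 one-sided (70). The stated 80 is not reproduced; 40 per arm gives 75.5% two-sided power. That is a separate matter, and nothing below depends on it.

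**What the contrast estimates.** With group, time and their interaction all free, the fitted means in complete data are the observed cell means. Write D and T for the arms and Y for the score.

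- Response is the score: the 36-month interaction is (mean Y_D36 − mean Y_D0) − (mean Y_T36 − mean Y_T0).
- Response is the change C = Y − Y_0: the baseline cells are zero, and the interaction is mean C_D36 − mean C_T36, which is the same quantity.

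A random intercept does not alter this estimate in complete data, and a site main effect cancels from within-child differences. A check on 8,000 simulated null trials per setting gave the same estimate and standard error under both readings.

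**Precision.** Per-child variance in units of SD²: change 2(1−r); baseline-adjusted 1−r². Their ratio is (1−r²)/[2(1−r)] = (1+r)/2. Power is two-sided at 38 vs 37 for a standardised effect of 0.6/√variance, taking 0.6 to be in raw-score SDs.

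| r | Change | Adjusted | Ratio | Power, change | Power, adjusted |
|---|---|---|---|---|---|
| 0.3 | 1.40 | 0.91 | 0.65 | 58% | 77% |
| 0.5 | 1.00 | 0.75 | 0.75 | 73% | 84% |
| 0.6 | 0.80 | 0.64 | 0.80 | 82% | 89% |
| 0.7 | 0.60 | 0.51 | 0.85 | 91% | 95% |
| 0.8 | 0.40 | 0.36 | 0.90 | 98% | 99% |
| 0.9 | 0.20 | 0.19 | 0.95 | about 100% | about 100% |

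The change contrast needs 1/0.75 − 1 = 33% more children at r = 0.5 for equal precision, 18% at 0.7 and 5% at 0.9. On CARS, with SD 7.05, the standard error is 7.05 × √[variance × (1/38 + 1/37)]: 1.63 vs 1.41 at r = 0.5, and 1.26 vs 1.16 at r = 0.7. The simulated variance ratios were 0.77 and 0.86 at those two values, close to the formula.

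**Effect of the observed baselines.** With no treatment effect, the expected change contrast given the baselines is −(1−r) × (baseline difference, DS1-EI minus TAU). The simulated slopes on the baseline difference were −0.50 at r = 0.5 and −0.30 at r = 0.7, against 0.00 for the adjusted analysis.

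- CARS, difference +1.1 (1.1/7.05 = 0.16 SD): 0.11, 0.33 and 0.55 points at r = 0.9, 0.7 and 0.5.
- PEP-3 imitation, difference −2.7 (about 0.37 SD): 0.27, 0.81 and 1.35 DQ points.

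DS1-EI started worse on both measures, so both shifts favour DS1-EI.

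**The case against.** The natural reading is an ordinary repeated-measures model on the score, with *change* naming what is studied. On that reading a reader cannot say that the baseline level holds only zeros, or that the log fallback is undefined. Those two points apply only if change is literally the response, and the plan also allows other transformations. This part of the objection stands.

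A reader might also infer that the planned effect is biased, or that it carries the baseline imbalance through. It does neither. It is unbiased over randomisation, and it subtracts the whole baseline difference. What remains is a conditional over-correction of (1−r) times the chance imbalance. Nor does the plan flatly contradict itself: a baseline level with a participant effect does account for differing starting levels, though by subtraction only.

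The size is also open to challenge. With no r in the documents, the gain could be as little as 5% of variance, and from r = 0.6 upward the planned contrast already passes 80% power under the raw-SD reading. Imitation is the largest of the six PEP-3 imbalances, and the CARS shift is small against an SD of 7. It is tempting to say that below r = 0.5 the plan does worse than the t-test used for sizing. That needs the 0.6 to be in raw-score SDs, which the protocol does not say. If the 0.6 is in SDs of change, the change contrast has that t-test's power whatever r is.

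Dyads were matched on sex, age and developmental quotient, which limits imbalance but does not put the inclusion score into the model. Even with exactly balanced baselines, where the two estimates coincide, the change analysis would report the larger standard error. The absence of significant baseline differences does not answer the point for the same reason. Covariance structure and residual checks are normal SAP detail and form no part of this point.

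**Conclusion.** The point holds in a limited form. As specified, and with complete data, the treatment effect is the difference in mean change under either reading of the response. It is a valid estimate, but not the most precise one available. Conditioning on the inclusion score would cut its variance by 25% at r = 0.5, 15% at r = 0.7 and 5% at r = 0.9. If the 0.6 is in raw-score SDs, power at 38 vs 37 would rise from about 73% to 84%, or from 91% to 95%, at the first two of these values. The conditional shift towards DS1-EI is small on CARS and moderate at most on imitation. All these sizes rest on an assumed r and on equal SDs at baseline and 36 months. The equality of the contrast with the difference in mean change does not depend on r. Where data stay incomplete after carrying observations forward, that equality is only approximate.

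**What to change.** State that the response is the observed score at each visit. Then do one of the following:

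- model the 18- and 36-month scores with the inclusion score, by time, as a covariate; or
- model all three visits with the baseline means constrained equal between arms, so that group differences enter only after baseline.

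Report the adjusted 36-month difference as the effect. If change is kept as the response, do not log-transform it, since it can be zero or negative. Table 3 already schedules CARS and PEP-3 at inclusion, so the cost is a few sentences of wording, with no new data and no change to the design.

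### The sample size is powered for a two-group t-test, while efficacy is to be read from a group × time interaction over three visits with no deciding contrast named

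*Protocol article*

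**What the plan says.** Number of Participants fixes the inputs "for a moderate effect size (α = 0.6), a power fixed at 80" per cent with p below 0.05, and concludes that "80 patients randomized into two groups are required for a student" t-test. The next sentence sets the recruitment range: "Given our choice to use linear mixed models (see below) to take into account participant’s effect, we planned to recruit from 70 to 80 participants". No power is given for the mixed model.

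Statistical Analysis explains change in each primary and secondary variable by group exposure, "time (baseline vs. 18 vs. 36 months) and their interaction (group exposure × time", plus a random effect and a site effect. It says this regression should account for the change specific to DS1-EI. It does not say whether the interaction is tested jointly or visit by visit, or which visit decides.

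Two other places bear on the choice of visit. The abstract has the primary variables assessed blind at both 18 and 36 months. Participants and Recruitment sets the trial duration at 36 months and describes the 12-, 18- and 24-month assessments as intermediate.

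**The concern.** A two-group t-test is a single 1-df comparison. Group × time with three listed time levels is, on its natural reading, a joint 2-df hypothesis: that the two groups' profiles are parallel over baseline, 18 and 36 months. The stated power therefore describes a different test from the analysis.

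Two things are at stake. The first is interpretation. Any departure from parallel profiles can reject the joint hypothesis, including an 18-month difference that is gone at 36 months, so a significant result would not by itself show benefit at the end of the 36-month intervention. The second is power. If benefit builds steadily, the second degree of freedom costs power that a single 36-month contrast from the same model would keep.

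**Working it through.** **Inputs from the article.** Effect size 0.6, power 80%, p < 0.05, 80 patients (taken as 40 per arm); 38 and 37 children enrolled; time at baseline, 18 and 36 months.

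**Assumptions, because the article gives no figure.** Two-sided testing; equal correlation between visits (compound symmetry); complete data; site effect ignored; 0.6 first taken in SDs of the 0–36 month change, then in raw-score SDs.

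**Step 1. The printed figure.** With d = 0.6, two-sided 0.05 and 40 per arm, the exact noncentral t gives 75.5% power, not 80%; 45 per arm (90 in all) are needed. One-sided, 36 per arm (72) suffice and 40 per arm give 84.5%. Neither version returns 80 patients; 40 per arm give 80% two-sided only at d = 0.634.

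**Step 2. Noncentrality.** Under equal correlation ρ, each change from baseline has variance 2σ²(1 − ρ), and the 18- and 36-month changes have covariance σ²(1 − ρ). Their correlation is 0.5 whatever ρ is. Let a and b be the group differences in change at 18 and 36 months, in SDs of change, and let m = 38 × 37 / 75 = 18.75.

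- 1-df 36-month contrast: λ = m b²
- 2-df interaction: λ = m (a² − ab + b²) / 0.75

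Power comes from the noncentral F with denominator df 2 × (75 − 2) = 146.

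**Step 3. Change-score scale, 38 and 37 children.** For the first four rows b = 0.6, so the 1-df λ is 18.75 × 0.36 = 6.75.

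| Shape of benefit | a, b | 2-df λ | 2-df power | 36-month contrast |
|---|---|---|---|---|
| Linear | 0.3, 0.6 | 6.75 | 62.9% | 73.3% |
| 70% by 18 months | 0.42, 0.6 | 7.11 | 65.3% | 73.3% |
| Complete by 18 months | 0.6, 0.6 | 9.00 | 76.2% | 73.3% |
| Only after 18 months | 0, 0.6 | 9.00 | 76.2% | 73.3% |
| Transient: 18 months only | 0.6, 0 | 9.00 | 76.2% | 5.0% |

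At 40 per arm with linear accrual (λ = 7.2), the figures are 66.0% and 76.0%.

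**Step 4. Raw-score scale.** If 0.6 is in SDs of the score, λ for linear accrual becomes 6.75 / [2(1 − ρ)] for both tests. With 38 and 37 children:

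| ρ | 2-df power | 36-month contrast | Gap (points) |
|---|---|---|---|
| 0.3 | 48% | 59% | 11 |
| 0.5 | 63% | 73% | 10 |
| 0.6 | 73% | 82% | 9 |
| 0.7 | 85% | 91% | 6 |
| 0.8 | 96% | 98% | 2 |

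**Step 5. Against the t-test used for sizing.** A t-test on 36-month scores with d = 0.6 and 38 and 37 children has 73% power. On the raw-score scale the 2-df test is weaker at ρ = 0.5 or below, about equal near 0.6, and stronger at 0.7 or above.

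**The case against.** The strongest answer is that Statistical Analysis lists model terms and never says efficacy rests on a joint 2-df test. The same model yields separate 18- and 36-month group terms, and an analysis plan not shown here may name one of them. That stands: 2 df is the natural reading of three listed levels, not a stated rule. It does not remove the mismatch, because the article itself states both the sizing test and the model and links them without a power figure for the model.

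Several stronger readings are tempting but unsupported:

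- **That the trial loses ten points from its printed 80%.** The ten points lie between two tests within one model. The comparison with the t-test turns on a correlation the article omits, and 80% is not reproduced in any case.
- **That gradual accrual is the trial's hypothesis.** The Discussion explains the long duration by the risk of failure with typically small effects, and states no shape over time.
- **That the article claims the mixed model permits a smaller sample.** Its stated purpose is to account for the participant's effect, and the 70–80 range includes 80.

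It can also be said that making 36 months decisive is a preference, since the primary variables are measured blind at both visits. But the article defines the trial as 36 months and calls the 18-month assessment intermediate, which supports the choice.

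**Conclusion.** The concern holds in a limited form. Power is stated for a t-test, the analysis is a three-level group × time interaction, and no deciding contrast is named.

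The interpretive problem does not depend on how benefit accrues: on the change-score scale, a 0.6 SD difference at 18 months that disappears by 36 months would make the joint test significant about 76% of the time.

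The power cost is conditional. It is about 10 points (63% against 73%) under linear accrual, equal correlation and change-score scaling, and about 2 to 11 points over correlations 0.8 to 0.3 on raw-score scaling. It reverses by about 3 points on the change-score scale if benefit is complete by 18 months or appears only later. Whether the joint test is weaker or stronger than the printed t-test cannot be settled from the article.

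**What to change.** In Statistical Analysis, name as the efficacy test the DS1-EI minus TAU difference in change from baseline to 36 months, estimated from the same mixed model with a 95% CI. Report the 18-month contrast and the joint 2-df interaction as supportive.

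In Number of Participants, do not attach the printed 80% to this contrast. Restate its power with the assumed scale and correlation shown: about 73% with 38 and 37 children, and 76% at 40 per arm, if 0.6 is in SDs of change.

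The cost is a few sentences, with the same model and data. The downside is about 3 points of power under equal correlation if benefit is complete by 18 months or appears only afterwards. It would be larger if correlation decays between visits: with first-order autoregressive correlation of 0.3 to 0.8, raw-score scaling, 40 per arm and a large-sample calculation, it is about 6 to 13 points. That is one more reason to state the assumed correlation.
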